**Discussion:**

This study has been designed to determine (i) whether EUS-FNB using 22G Franseen needle with dry suction is non-inferior to wet suction in terms of diagnostic accuracy and (ii) the optimal number of passes during EUS-FNB of SPLs using 22G Franseen needle.

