## Methods

### Study design

This is a multicenter, open-label, randomized controlled non-inferiority trial with two parallel groups. Two hundred patients with SPLs will undergo EUS-FNB using 22G Franseen needles in 4 tertiary Chinese hospitals and will be randomly assigned to the dry suction group and the wet suction group in a ratio of 1:1. A checklist with the recommendations for Interventional Trials (SPIRIT) is attached as Additional file 1. Study flowchart and standard protocol items displaying the trial’s enrollment, intervention, and assessment schedules were showed in Figs. 1 and 2, respectively.

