### Outcomes

The primary outcome is to compare the rate of diagnostic accuracy of EUS-FNB using the two different suction techniques (dry suction and wet suction). The rate will be calculated as the sum of true positive values and true negative values divided by the total number of samples, with an accurate diagnosis defined as a final diagnosis consistent with the tissue sample obtained during the needle passes.

The secondary outcomes include the optimal number of needle passes, sensitivity, specificity, specimen quality, cytological diagnoses, time of the procedure, and incidence of complications. Specificity analysis is only applicable to participants without malignancy, whereas sensitivity analysis is only applicable to persons with malignancy.

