### Sample size calculation

The sample size calculation was based on the primary outcome of diagnostic accuracy for the evaluation of solid pancreatic lesions. The reported diagnostic accuracy of EUS-FNB for SPL using dry suction is approximately 96.2%, and the wet suction technique is about 98.3% in the literature [6, 8]. Based on the reported data and the clinical judgment, the non-inferiority of dry suction in EUS-FNB will be assessed with a non-inferiority (*δ*) margin of 10%. With a two-sided test, a significance level of 2.5% (*α* = 0.025), and a power (1 − *β*) of 90%, using the PASS 15.0 software and a sample allocation ratio of 1:1 between the dry suction and wet suction groups, 180 patients should be enrolled. Considering a 10% dropout rate, a final sample of 200 participants (100 per group) is needed.

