### Statistical analysis plan

The full analysis set should be as close as possible to the intention-to-treat set. The direct deletion method will be used to treat missing data.

Continuous variables will be summarized as means with standard deviation and compared with *t*-tests or Wilcoxon rank-sum tests. Categorical variables will be expressed as percentages using the *χ*^2^ test or the Fisher exact test. Differences in diagnostic yield between the two techniques will be evaluated with the chi-squared test. Statistical significance will be considered for *P* < 0.05. All statistical analyses will be performed using SPSS (version 25.0, IBM, Armonk, NY).

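### The trial is sized to test dry suction against a 10-point non-inferiority margin, but its analysis section names only tests of equality at P < 0.05

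*Protocol article*

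**What the plan says.** The design is fixed in the protocol article under Study design: "This is a multicenter, open-label, randomized controlled non-inferiority trial with two parallel groups". The abstract's Discussion paragraph gives the question as "whether EUS-FNB using 22G Franseen needle with dry suction is non-inferior to wet suction in terms of diagnostic accuracy". Under Outcomes, "The primary outcome is to compare the rate of diagnostic accuracy of EUS-FNB using the two different suction techniques".

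The Sample size calculation section says "the non-inferiority of dry suction in EUS-FNB will be assessed with a non-inferiority" margin of 10%. It takes planning accuracies of 96.2% for dry and 98.3% for wet suction, alpha 0.025 (described as two-sided) and 90% power. It arrives at 180 patients, or 200 after 10% dropout.

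The next section on statistics, Statistical analysis plan, says "Differences in diagnostic yield between the two techniques will be evaluated with the chi-squared test". Just before that it gives a general rule for categorical variables, the chi-squared or Fisher exact test, and it sets significance at P < 0.05. It mentions no margin, no confidence interval, no non-inferiority hypothesis and no 0.025 level.

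**The concern.** The two sections describe different hypothesis tests. A chi-squared or Fisher test has as its null hypothesis that dry and wet accuracy are equal. The null hypothesis that a non-inferiority trial must reject is that dry suction is at least 10 points worse.

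A non-significant equality test does not show that a 10-point deficit has been ruled out. A significant one does not show that the deficit reaches 10 points. Carried out as written, the analysis ends in either a significant difference or no significant difference, and neither is the conclusion the trial was set up to reach. The main danger is that a non-significant P value is reported as non-inferiority.

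**Working it through.** **Inputs.** Dry 96.2%, wet 98.3%, margin 10% (read as 10 percentage points), alpha 0.025, power 90%, 1:1 allocation, 10% dropout: all from Sample size calculation. Equality test and P < 0.05: from Statistical analysis plan.

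**1. Reproduce the stated sample size.** With unpooled variance and one-sided alpha 0.025,

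n per arm = (1.960 + 1.282)² × [0.962 × 0.038 + 0.983 × 0.017] / (0.10 − 0.021)²

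= 10.507 × 0.05327 / 0.006241 = 89.7, so 90 per arm and 180 in total. Then 180 / 0.90 = 200.

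The stated figures come back exactly, with the margin in the denominator and a one-sided 0.025 level. A true two-sided 2.5% test (one-sided 0.0125) would give 212. So the sample size belongs to a margin test at one-sided 0.025, which the analysis section does not name.

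**2. How the rules behave when dry suction is exactly 10 points worse.** For each rule, sum over all outcome pairs (x dry, y wet):

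Probability = Σx Σy Bin(x; n, p_dry) × Bin(y; n, p_wet) × 1[rule met at (x, y)].

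The wet rates 98.3% and 96.2% are the article's two planning figures; 95% is an assumption to widen the range. The dry rate is set 10 points lower. With n = 90 per arm:

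| True accuracy, dry v wet | Chi-squared P ≥ 0.05 | Score test passes −10 points | Wald 95% interval passes −10 points |
|---|---|---|---|
| 88.3% v 98.3% | 19.2% | 2.2% | 4.6% |
| 86.2% v 96.2% | 31.3% | 2.4% | 3.5% |
| 85% v 95% | 36.8% | 2.4% | about 3% |

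With 100 per arm the chi-squared column becomes 14.5%, 26.0% and 31.7%. A more conservative equality test makes non-significance more common: with the Yates correction the first entry rises from 19.2% to 29.6%.

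**3. A worked example.** Dry 84/90 v wet 89/90.
- Difference: 93.3% − 98.9% = −5.6 points.
- Chi-squared: pooled rate 173/180 = 0.9611; z = −0.0556 / √(2 × 0.9611 × 0.0389 / 90) = −1.93; P = 0.054. Fisher's exact P is 0.118.
- Wald 95% interval: standard error √[(0.0622 + 0.0110)/90] = 0.0285; lower limit −0.0556 − 1.96 × 0.0285 = −11.1 points.
- Score test against −10 points: z = 1.31, below 1.96; the score lower limit is about −12.9 points.

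The equality test reports no significant difference, while both intervals extend past −10 points. Non-inferiority is not shown.

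**4. At the planning rates (96.2% v 98.3%), 90 per arm.** In 15.1% of trials the chi-squared test is non-significant although the score interval does not exclude −10 points. Exact power to show non-inferiority is 73% with the score rule and 86% with the Wald rule; with 100 per arm it is 77% and 87%.

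**The case against.** **The margin is in the article.** A reader might infer that the trial has no margin-based criterion at all. That goes too far. The sample size section states the margin and says non-inferiority will be assessed with it. The fault is a contradiction between two sections. An article may also leave the interval method to a fuller plan. But this one does name tests for the comparison, and they test another hypothesis, so it is more than an omission.

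**The quoted sentence concerns yield, and the primary outcome is accuracy.** If the two differ, no test is tied specifically to the primary outcome, and the general chi-squared or Fisher rule for categorical variables applies. That is still a test of equality, so the conclusion is the same on either reading.

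**The error rates depend on a reading.** One might take 19–37% as the trial's false-positive rate. The article never says that P ≥ 0.05 will be declared non-inferior, so these figures are conditional on that reading.

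**Small counts are provided for.** Few inaccurate diagnoses are expected, and a reader of the chi-squared sentence alone might think no alternative is offered. The preceding sentence allows Fisher's exact test.

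**The opposite conflict is rare.** A reader might expect significant P values often to overturn results that meet the margin. At the planning rates, a significant chi-squared result together with a score limit above −10 points occurs in 0.2% of trials at 90 per arm and 3.8% at 100. With counts that small, Fisher's test may not be significant at all. This direction carries little weight.

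**Conclusion.** The point stands as an internal contradiction that must be resolved. The design, the stated question and the sample size all rest on a 10-point margin at one-sided 0.025. The analysis section names only equality tests at P < 0.05, which cannot deliver that conclusion whatever their result.

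If a non-significant P value were taken as non-inferiority, the false claim rate at 90 per arm would be about 19–37% when dry suction is truly 10 points worse, against about 2–5% for a margin-based interval. This assumes independent binomial outcomes, an absolute margin, and true accuracies in the range tabulated. The documents do not support saying that the margin is missing, that this misreading is planned, or that correcting the analysis leaves the stated 90% power intact.

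**What to change.** Amend the Statistical analysis plan section to say that:
- the primary analysis estimates the difference in diagnostic accuracy, dry minus wet, with a two-sided 95% confidence interval by a method named before database lock;
- non-inferiority is concluded only if the lower limit is above −10 percentage points (one-sided alpha 0.025);
- chi-squared or Fisher P values for this comparison are descriptive.

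In Sample size calculation, change the wording "With a two-sided test, a significance level of 2.5" per cent to agree with this, since 180 reproduces at one-sided 0.025.

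The change is a paragraph of wording and needs no new data items, but it has two costs. Some results that would have read as no significant difference will be reported as non-inferiority not shown. And power depends on the interval chosen. A score interval holds the 2.5% error rate but has exact power of about 73% (90 per arm) to 77% (100 per arm) at the planning rates. A Wald interval has about 86–87%, with an error rate of about 3–5%. The stated 90% comes from a normal approximation and should be restated for the method chosen. A sample size calculation using the Farrington–Manning null variance gives 284 patients in place of 180, so the choice should be made knowingly and before results are seen.

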### Monitoring

A data monitoring plan and detailed routine verifications of the CRFs will be proposed. An independent data monitoring committee (DMC) is established to ensure the safety and efficacy of the trial. The DMC will regularly review the progress of the trial, including recruitment, data collection and analysis, serious adverse events, etc., and provide advice to improve the quality.

If an adverse event occurs during the trial, the investigator must record the adverse event form, including the time, severity, duration, measures taken, and regression of the adverse event, and report to the ethics committee and regulatory authorities in time.

If an important modification to the study protocol is required for any reason, it will be approved in advance by the ethical committee. Investigators and participants will be notified of any significant protocol revisions.

### Publication of results

The trial results will be presented as abstracts at international gastrointestinal meetings, such as Digestive Disease Week and United European Gastrointestinal Week. We will publish the final data in a peer-reviewed medical journal to expand the dissemination.

## Discussion

There are several variables affecting the outcomes of EUS-FNA/FNB, including needle selection, operator experience, adequacy of sample, use of suction, the number of needle passes, and the presence of ROSE. Increasingly studies have reported that the Franseen needle can provide higher diagnostic yield and accuracy compared to other needle types, particularly for SPL [7, 9, 10]. The wet suction technique in EUS-FNA has been proven to reduce blood contamination and increase diagnostic yield [2, 3]. An RCT study found that EUS-FNB with wet suction resulted in a significantly better quality of specimen, histological, and first-pass diagnostic yields compared with the dry suction, but they used 5 ml negative pressure, which differed from the standard negative pressure previously reported [11]. Another study has shown that EUS-FNB using the slow pull, wet technique, or standard technique makes no significant difference in terms of specimen quality or the number of needles required to obtain a diagnosis. However, the study was a single-center study which was early terminated, resulting in inadequate sample size and convincing data [12].

In the previous RCT, dry suction versus wet suction was only compared during EUS-FNA procedure. There was no data for EUS-FNB using Franseen needle. In our study, we will compare the diagnostic accuracy of dry suction versus wet suction technique, and we also explore the optimal numbers of passes for SPLs. Smaller numbers of needle passes will be beneficial to patients in terms of procedure time, unnecessary passes, and risk of complications. We chose a non-inferiority design based on the expectation that dry suction of EUS-FNB is as good as wet suction and the dry suction can simplify the procedure and shorten the procedure time. With the improved performance of needles, satisfactory diagnostic accuracy of EUS-FNB in SLPs may be achieved only by dry suction and limited needle passes.

This study design has some limitations. First, this study will be performed in a multicenter setting; the bias between operators may still exist despite the training on standardized processes for all centers. Large sample size and randomization have been used to counteract this possible bias and to obtain results that allow for extrapolation to the general population.

Second, surgical pathological data was not available in all patients with SPLs. Some patients do not undergo surgery because the lesion is benign or because they refuse surgical treatment. Thus, clinical and imaging follow-up will be done for at least 12 months to determine the final diagnosis.

In conclusion, this is the first multicenter randomized controlled trial designed to clarify whether the dry suction technique is non-inferior to the wet suction technique and the optimal needle passes for SPLs using a 22G Franseen needle. The findings may provide high-level evidence of EUS-FNB procedures in clinical practice.

## Trial status

Protocol version number: 1.0, May 26, 2022.

Patient recruitment was initiated in September 2022 and is estimated to be completed by June 2024. At present (October 13, 2023), 123 patients have been enrolled in the study.

## Data Availability

The case report form is stored in the Nanfang Hospital. The individual data of each patient will be stored in each center and will not be available to the public because of “Protection of Personal Data.” The principal investigators will be given access to the cleaned datasets, and the data can be available via contacting PI if requested.

## Abbreviations

EUS: Endoscopic ultrasonography
EUS-FNA: Endoscopic ultrasound-guided fine-needle aspiration
EUS-FNB: Endoscopic ultrasound-guided fine-needle biopsy
FNA: Fine-needle aspiration
SPLs: Solid pancreatic lesions
CT: Computed tomography
MRI: Magnetic resonance imaging
INR: International normalized ratio
CA-199: Carbohydrate antigen 19–9
MOSE: Macroscopic onsite evaluation
